### 2.8. Safety Assessment

Any adverse events (AEs) that occur during the study period will be reported to the research assistants, and the causality between AE and drug will be assessed according to the WHO Uppsala Monitoring Center System for Standardized Case Causality Assessment [34]. Laboratory examinations including the blood routine test, urine routine test, liver function, kidney function, coagulation function, and electrocardiogram will be performed at the baseline and the fourth week. Attention is paid to the abnormal changes of laboratory test results, they are recorded as an AE if they have clinical significance, and the causality with the study drug is assessed.

An independent Data and Safety Monitoring Committee (DSMC) will also evaluate the safety data which will be requested during the trial. Severe AEs (SAEs) or severe adverse reactions (SARs) are defined according to the International Council for Harmonization of Technical Requirements for Pharmaceuticals for Human Use (ICH) guidelines [35]. They must be reported to the DSMC, the GPHCM ethnics committee, and the research team within 24 h. AE or SAE details such as occurrence, severity, management, and causality to the intervention will be recorded on electric case report forms (eCRFs). In emergency situations, physicians will be consulted, and the blinding will be broken if necessary.

### 2.9. Sample Size

The sample size was calculated based on a mean change of 4.46 with a standard deviation (SD) of 1.5 scores in the XFZY group [36], a mean change of 2.14 with an SD of 1.5 scores in the placebo group [37], and the minimal clinically important difference set to 1.7 [38]. A sample size of 87 patients per group was determined to provide 80% power to achieve statistical significance at the 5% 2-sided level and a superiority margin of 1.7 for comparisons of XFZY and placebo for the primary outcome. This calculation allowed for a 15% rate of withdrawal and loss to follow-up.

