**Methods:**

This multicenter, double-blind, randomized, placebo-controlled trial will be undertaken in China. A total of 174 eligible participants will be randomly assigned to either an XFZY group or a placebo group (20 ml each dose, three times daily for 4 weeks) at a ratio of 1 : 1. The primary outcome is the change in mean headache intensity measured by a 10 cm visual analogue scale (VAS). Secondary outcomes include the area-under-the headache curve (AUC), headache frequency, rescue medication use, *qi-stagnation and blood-stasis* pattern measurement, quality of life measured by the EuroQol-5-Dimensions-5-Level (EQ-5D-5L), global evaluation of medication, and health economic indexes. *Discussion*. The results of the study are expected to provide evidence of high methodological and reporting quality on the efficacy and safety of XFZY for TTH. This trail is registered with ChiCTR1900026716 (registered on 19 October, 2019).

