### 2.10. Statistical Analysis

The statistical analysis will be performed on the basis of a pre-established statistical analysis plan. Data analysis will be based on the intent-to-treat (ITT) and per protocol (PP) principles and will be conducted by independent qualified statisticians blinded to treatment allocation. Two-tailed *p* values less than 0.05 will be considered statistically significant. Missing data will be replaced by the multiple imputation method. All analyses will be conducted with SPSS version 18.0 (IBM SPSS Inc, Armonk, New York, USA) or SAS 9.2 (SAS Institute Inc., Cary, USA). Continuous variables will be expressed as mean ± SD if data are normally distributed. Data not normally distributed will be presented using the median and interquartile range (IQR). Categorical variables will be expressed as counts and percentages.

For primary and secondary outcomes, a full analysis set including participants with at least one treatment and outcome assessment and a perprotocol analysis set containing 4-week treatment,will be employed to compare the changes between groups with an independent *t*-test, respectively; repeated measures of analysis of variance or a liner mixed model will be applied to analyze the changes measured at different time points. Sex, age, course of disease, and center, as well as other covariates will be considered in the statistical model.

For safety assessments, a safety analysis set with all subjects who took the drug at least once will be adopted to detect whether the AE proportions are significant between the two groups. This will be performed with either a *χ*^2^ test or Fisher's exact test. All AEs will be coded based on the Chinese version of the Medical Dictionary for Regulatory Activities (MedDRA).

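### 87 patients per group do not give 80% power at the two-sided 5% level; against the 1.7 margin, power after the planned losses is about 70%

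*Protocol article*

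**What the plan says.** Section 2.9 (Sample Size) of the protocol article gives every input. For the active arm it assumes "a mean change of 4.46 with a standard deviation (SD) of 1.5 scores in the XFZY group"; for placebo it assumes a mean change of 2.14 with the same SD. The design claim is "A sample size of 87 patients per group was determined to provide 80% power to achieve statistical significance at the 5% 2-sided level", with 1.7 as the margin for superiority on the primary outcome. Losses are already inside the 87: "This calculation allowed for a 15% rate of withdrawal and loss to follow-up".

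The rest of the article agrees on size and level. The Methods part of the abstract has "A total of 174 eligible participants will be randomly assigned", which is 2 × 87, and Section 2.1 gives 1:1 allocation. Section 2.10 (Statistical Analysis) names an independent t-test on the changes and sets the level: "Two-tailed *p* values less than 0.05 will be considered statistically significant". No one-sided test is mentioned anywhere in the article.

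**The concern.** Level, sidedness, power, effect, SD, margin, attrition and sample size are all stated together, so they can be checked against each other, and they do not agree. The sample size is too small for the two-sided level that Sections 2.9 and 2.10 both declare.

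Power tells readers how to interpret a result that fails to clear the margin. Such a result would be taken as coming from a trial with a 20% chance of missing the assumed effect, when on the article's own assumptions the chance is close to 30%.

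**Working it through.** **Inputs** (Section 2.9 unless noted)

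- Mean changes 4.46 and 2.14, so the assumed difference is 4.46 − 2.14 = 2.32
- Superiority margin 1.7, so the excess over the margin is Δ = 2.32 − 1.7 = 0.62
- SD σ = 1.5 in both groups; standardised excess 0.62/1.5 = 0.413
- Power 80% (z = 0.8416); two-sided 5% (z = 1.9600)
- Loss 15%; allocation 1:1 (Section 2.1); independent t-test (Section 2.10)

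**Formula.** Evaluable patients per group: n = 2(z_α + z_β)²σ²/Δ². Randomised per group: n/(1 − 0.15).

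**Reproducing the plan's 87**

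- One-sided 5%, normal: 2 × (1.6449 + 0.8416)² × 2.25/0.3844 = 72.4, so 73; 73/0.85 = 85.9, so 86.
- One-sided 5%, noncentral t: 74; 74/0.85 = 87.06. This is the stated 87 to the nearest whole number (strict rounding up gives 88).
- No margin, two-sided 5%: a difference of 2.32 needs 7 evaluable, 9 after loss; a difference of 1.7 needs 13 evaluable, 16 after loss. Neither is near 87.

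Of the variants tried, only a one-sided 5% test against the 1.7 margin lands on or next to 87. That this is what was done is an inference from the match; the article does not say so.

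**The stated design, two-sided 5%**

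- Normal: 2 × (1.9600 + 0.8416)² × 2.25/0.3844 = 91.9, so 92; 92/0.85 = 108.2, so 109 per group (218 in total).
- Noncentral t: 93; 93/0.85 = 109.4, so 110 per group (220 in total).

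**Power of the planned trial at two-sided 5%.** Normal approximation: Φ(Δ/(σ√(2/n)) − 1.96).

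- After loss, 87 × 0.85 = 73.95, so n = 74: Φ(0.62/0.2466 − 1.96) = Φ(0.554) = 71.0%. Noncentral t: 70.5%.
- No loss, n = 87: Φ(0.62/0.2274 − 1.96) = Φ(0.766) = 77.8%. Noncentral t: 77.4%.

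For comparison, one-sided 5% with n = 74 gives 80.8% (normal) or 80.45% (t), which is the advertised power.

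**Type II error (t).** With 74 evaluable it is 29.5%, or 29.5/20 = 1.48 times the stated value. With all 87 it is 22.6%, or 1.13 times.

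**The case against.** **The 70% figure assumes that the lost 15% contribute nothing.** Section 2.10 plans intention-to-treat analysis, multiple imputation, possibly a mixed model, and covariates. These could recover something, so 70% is the value for an unadjusted t-test on 74 completers per group. This qualification stands, but it does not rescue the claim: even with all 87 fully observed, the unadjusted test reaches only 77 to 78%, and imputation does not restore all the lost information. Covariate adjustment could raise power, but Section 2.9 takes no credit for it and gives no correlation from which to calculate the gain.

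**The test may really be against zero.** Section 2.10 does not repeat the margin, and under the same assumptions a test of no difference has power above 99%. The shortfall therefore matters in practice only if the margin test is the one carried out. This limit is real. But Section 2.9 ties its 80% to the 1.7 margin, so the statement is wrong as written. If zero is the intended null value, Section 2.9 describes a different test and still needs correcting.

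**A one-sided 5% test may have been intended.** Then the arithmetic is nearly right, and both sections misstate the error rate. One or the other has to change.

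**It is only a reporting error.** No patient, measurement or false-positive rate is affected under the stated two-sided level. That is fair as to cost, but the misstated item is the justification of the trial's size for its primary outcome.

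**Conclusion.** The concern holds. With the article's own inputs, 87 randomised per group do not provide 80% power at the two-sided 5% level against a margin of 1.7. Power is about 70% (70.5% by t, 71.0% by the normal approximation) with 74 evaluable per group, and 77 to 78% if nobody is lost. Delivering the stated 80% would take 218 to 220 patients in place of 174, that is 44 to 46 more.

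This rests on the difference of 2.32, SD 1.5, the 1.7 margin, 1:1 allocation and an unadjusted two-group t-test, all stated in the article. The 70% figure also takes the planned 15% loss as fully uninformative. The mismatch itself does not depend on that last assumption. Nor does it depend on how the error arose, although the number is consistent with a one-sided 5% t-based calculation.

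**What to change.** Correct the power statement in Section 2.9, and wherever the statistical analysis plan repeats it. Suggested content: with 87 randomised and 74 evaluable per group, power to show superiority over the 1.7 margin is about 70% at the two-sided 5% level, and at most 77 to 78% without losses; 80% is reached only at a one-sided 5% level. Keep 174 patients and the two-sided 5% level. In the same edit, say in Section 2.10 whether the primary test is against 1.7 or against zero.

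The cost is one or two sentences and a less favourable power figure, with no extra patients. This discloses the shortfall; it does not remove it. If 80% is wanted, there are two routes:

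- **More patients:** 109 to 110 per group, 218 to 220 in total.
- **A baseline-adjusted primary analysis with a stated, justified correlation.** By the normal formula, 80% power with 74 evaluable per group needs a residual SD of 1.346. Baseline would have to explain 1 − (1.346/1.5)² = 0.195 of the variance of the change, a correlation of about √0.195 = 0.44 between baseline and change. The article gives no such figure, so this is a target to be supported with data and cannot simply be assumed.

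Rewording the text to a one-sided 5% level would make the numbers agree, but it would double the false-positive rate in favour of XFZY from 2.5% to 5%, and is not recommended.

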### 2.10. Statistical Analysis

The statistical analysis will be performed on the basis of a pre-established statistical analysis plan. Data analysis will be based on the intent-to-treat (ITT) and per protocol (PP) principles and will be conducted by independent qualified statisticians blinded to treatment allocation. Two-tailed *p* values less than 0.05 will be considered statistically significant. Missing data will be replaced by the multiple imputation method. All analyses will be conducted with SPSS version 18.0 (IBM SPSS Inc, Armonk, New York, USA) or SAS 9.2 (SAS Institute Inc., Cary, USA). Continuous variables will be expressed as mean ± SD if data are normally distributed. Data not normally distributed will be presented using the median and interquartile range (IQR). Categorical variables will be expressed as counts and percentages.

For primary and secondary outcomes, a full analysis set including participants with at least one treatment and outcome assessment and a perprotocol analysis set containing 4-week treatment,will be employed to compare the changes between groups with an independent *t*-test, respectively; repeated measures of analysis of variance or a liner mixed model will be applied to analyze the changes measured at different time points. Sex, age, course of disease, and center, as well as other covariates will be considered in the statistical model.

For safety assessments, a safety analysis set with all subjects who took the drug at least once will be adopted to detect whether the AE proportions are significant between the two groups. This will be performed with either a *χ*^2^ test or Fisher's exact test. All AEs will be coded based on the Chinese version of the Medical Dictionary for Regulatory Activities (MedDRA).

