### 2.3. Randomization

A block randomization sequence stratified by centers is generated by SAS 9.2 (SAS Institute Inc., Cary, USA) and performed by the Institute of Basic Research in Clinical Medicine (IBRCM), China Academy of Chinese Medical Sciences, through an interactive web response system. When eligible patients who have signed informed consent forms are enrolled, an independent researcher will log into the system to obtain their allocation results. The randomization results will be kept confidential and maintained by IBRCM. All patients and researchers, including investigators, outcome assessors, statisticians, and other staff involved in the trial will be unaware of the grouping and treatment during the study period.

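### The only between-group test named for VAS change is an unadjusted t-test, which uses neither baseline VAS nor the stratification factor, centre; name one adjusted primary analysis

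*Protocol article*

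**What the plan says.** The primary outcome (section 2.7.1) is the change in mean headache intensity on a 10 cm VAS from baseline to the end of week 12. Table 2 schedules VAS at weeks 0, 1, 2, 4, 8 and 12.

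Section 2.10 covers the analysis in three steps:

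- The full analysis set and the per-protocol set "will be employed to compare the changes between groups with an independent" t-test. The former is "a full analysis set including participants with at least one treatment and outcome assessment".
- For change over several visits, "repeated measures of analysis of variance or a liner mixed model will be applied".
- On covariates: "Sex, age, course of disease, and center, as well as other covariates will be considered in the statistical model". Baseline VAS is not in this list.

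Section 2.3 describes the allocation: "A block randomization sequence stratified by centers". Section 2.9 plans for "a mean change of 4.46 with a standard deviation (SD) of 1.5 scores in the XFZY group", "a mean change of 2.14 with an SD of 1.5 scores in the placebo group" and "a superiority margin of 1.7 for comparisons of XFZY and placebo for the primary outcome", with 87 per group, 80% power, two-sided 5% and 15% loss.

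**The concern.** A two-sample t-test takes no covariates. Used on change scores, it fixes the coefficient of baseline at 1 instead of estimating it, and it leaves centre out although centre was balanced by design. If centres differ in outcome, the t-test's standard error is then larger than it needs to be.

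The sentence on covariates could remedy this, but it refers to a model that the article does not connect to the t-test. As written, the t-test is the method named for comparing the groups, the repeated-measures ANOVA or mixed model is named for the time course, and covariates apply to an unspecified model. A reader cannot tell whether the primary estimate is adjusted, or whether it comes from the t-test or from a model.

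Precision is at stake. If the trial is meant to show a benefit beyond the 1.7 cm margin, its planned power is limited and wasted precision counts.

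**Working it through.** **Inputs from section 2.9.** Planned difference 4.46 − 2.14 = 2.32. Distance above the margin 2.32 − 1.7 = 0.62. SD of change 1.5. Evaluable per group 87 × 0.85 ≈ 74.

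**The plan's own figure.** With the normal approximation, n per group = 2 × [1.5 × (z for alpha + z for power) / 0.62]².

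- Two-sided 5%, as stated: 2 × [1.5 × (1.960 + 0.842) / 0.62]² = 91.9, so 92 evaluable and 92 / 0.85 → 109 randomised per group. The stated 87 is not reproduced.
- One-sided 5%: 2 × [1.5 × (1.645 + 0.842) / 0.62]² = 72.4, so 73 evaluable and 86 randomised. With the t distribution it is 74 evaluable, and 74 / 0.85 = 87.06. This matches 87.

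**Unadjusted power at 74 per group, two-sided 5%.** The standard error is 1.5 × √(2/74) = 0.247 and the noncentrality is 0.62 / 0.247 = 2.51. Power is 70.5% (noncentral t, also used for all power figures below). Against a zero difference, with effect 2.32, power exceeds 99.9%.

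**Effect of adjusting for baseline.** Let r be the correlation of baseline with week-12 VAS and k = baseline SD / week-12 SD. With a common slope and in large samples:

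variance ratio (ANCOVA / change score) = (1 − r²) / (1 + k² − 2rk).

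Denominator minus numerator is k² − 2rk + r² = (k − r)², which is never negative. So the ratio never exceeds 1, and it equals 1 only when r = k. With k = 1 it reduces to (1 + r)/2.

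The article gives neither r nor k, so both are assumptions here. Power uses SD = 1.5 × √ratio:

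| k | r | Variance ratio | Power against the margin |
|---|---|---|---|
| 1.0 | 0.3 | 0.65 | 87% |
| 1.0 | 0.5 | 0.75 | 82% |
| 1.0 | 0.7 | 0.85 | 77% |
| 1.0 | 0.9 | 0.95 | 73% |
| 0.8 | 0.3 | 0.784 | 81% |
| 0.8 | 0.5 | 0.893 | 75% |
| 0.8 | 0.7 | 0.981 | 71% |
| 0.6 | 0.3 | 0.910 | 74% |
| 0.6 | 0.5 | 0.987 | 71% |
| 0.6 | 0.7 | 0.981 | 71% |

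With equal SDs, 80% is reached only for r up to about 0.6. A k below 1 is plausible because entry requires VAS of at least 3 cm (section 2.2), which narrows the baseline spread.

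**Effect of adjusting for centre.** If centre explains 2%, 5% or 10% of the variance of change (assumed), the ratio is 0.98, 0.95 or 0.90 and power is 71%, 73% or 75%.

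**The case against.** An unadjusted t-test on change is valid and unbiased in a randomised trial. The change score already subtracts baseline, though not with the best weight, and leaving out centre errs on the conservative side. Section 2.10 refers to a pre-established analysis plan, and a condensed article commonly leaves model terms to it. All of this stands. It limits the point to one of precision and clarity. It does not remove the point, because the article does not stay silent on the test: it names one, and the one named cannot carry the covariates it goes on to list.

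A reader might infer more than the article supports:

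- **That the plan ignores centre.** It does not. Centre is listed for the statistical model, and the words on other covariates do not exclude baseline VAS. What is missing is the link between that model and the t-test.
- **That the method could be picked after seeing the results.** The article states a pre-established plan and statisticians blinded to allocation, and it gives the t-test and the repeated-measures methods different purposes. Nothing shows an intention to choose later.
- **That adjustment would recover most or all of the lost power.** This depends on an r and k that the article does not give; recovery runs from almost none to all. The shortfall also comes from the sidedness in section 2.9, not from the t-test, and it exists only if the margin is tested. Section 2.10 mentions no margin.
- **That repeated-measures ANOVA would drop participants with a missing visit.** Section 2.10 specifies multiple imputation, which answers this.

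**Conclusion.** The point holds as one of efficiency and clarity. The named comparison uses neither baseline VAS nor centre, and its relation to the covariate-adjusted model is not stated. Adjustment for baseline does not cost precision in large samples, apart from a trivial loss of degrees of freedom, and may add some.

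If the 1.7 margin is tested at two-sided 5% with 74 evaluable per group, power moves from about 70% to between about 73% and 87% for r from 0.9 to 0.3 with equal SDs. It hardly moves when the baseline SD is smaller and close to r times the week-12 SD. These figures rest on assumed r and k, a common slope and the planned SD of 1.5. If the test is against zero, power exceeds 99.9% with or without adjustment, and the gain is only a narrower confidence interval.

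**What to change.** In section 2.10, name one primary analysis of the week-12 VAS change in the full analysis set: either ANCOVA or a linear mixed model for repeated measures over the scheduled visits. Include baseline VAS and centre as covariates and report the week-12 difference with its confidence interval. State that the t-test and the per-protocol results are supportive. Adding episodic versus chronic TTH as a covariate is optional.

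The cost is wording only, since VAS at week 0 and centre are already recorded.

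Separately, correct section 2.9 so that the sample size, the sidedness and the use of the 1.7 margin agree, and say in section 2.10 whether that margin is tested. Covariate adjustment should not be offered as a substitute for that correction.

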Chinese herbal medicine (CHM) has a long history in China and other regions of Asia. It is the main form of CM and could provide further options for headache treatment. The Chinese herbal formula Xuefu Zhuyu (XFZY) is the representative, classical CHM prescription for the treatment of headache. It has been widely used in the treatment of headache with *Qi-stagnation and Blood-stasis* pattern (QBS) (also called Zheng in CM). XFZY oral liquid is a patented product, which has been approved by the China Food and Drug Administration in 2002 (Ref No. Z10950063) [20]. It is an improved dosage form of XFZY decoction [21], which strictly follows the original prescription and dosage of XFZY decoction. Hence, they have the same function in promoting and activating the flow of *qi* and *blood* to treat QBS. This treatment has been utilized since the Qing Dynasty. XFZY consists of Bupleuri Radix (chaihu), Angelicae Sinensis Radix (danggui), Rehmanniae Radix (shengdihuang), Paeoniae Radix Rubra (chishao), Carthami Flos (honghua), Persicae Semen (taoren), Aurantii Fruxtus (zhiqiao), Glycyrrhizae Radix et Rhizoma (gancao), Chuangxiong Rhizoma (chuanxiong), Achyranthis Bidentatae Radix (niuxi), and Platycodonis Radix (jiegeng). A document to describe the components of the XFZY and pharmaceutical production processes were offered in supplementary file S1. Experimental studies have revealed that XFZY has an anticoagulating effect and improves microcirculation by reducing blood viscosity [22–25]. Clinical studies have shown that XFZY is effective in treating headache disorders, especially in migraine [26, 27], but the evidence of XFZY for TTH is absent. Therefore, the aim of this trial is to investigate whether the efficacy and safety of XFZY for TTH patients with QBS is superior to placebo.

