## 3. Discussion

To our knowledge, this is the first study to investigate the efficacy and safety of XFZY for TTH, compared to a placebo treatment. Although existing pharmacological and nonpharmacological treatments have been shown to be helpful [11, 41–43], the evidence available for treatment efficacy is limited to small magnitude or adverse events. Hence, new pharmacologic treatments are expected.

Both ETTH and CTTH patients are target populations of this study. However, they are categorized differently according to ICHD-3 criteria and have variant pathogenesis [44, 45]. Yet, the two diseases can be identified by the same CM pattern and are judged by similar signs and symptoms. QBS is a common TTH pattern. XFZY is a classical formula that promotes the flow of *qi* and *blood* in CM. Hence, we will conduct a randomized, double-blinded, placebo-controlled trial to evaluate the effect of XFZY for TTH with QBS.

Patient-centered outcomes are the focus of this study. This is in contrast to previous studies which have concentrated on rapid relief and being pain-free after 2 h, as recommended by HIS [31]. VAS and EQ-5D-5L are reported by the subjects, and the former is the primary outcome for evaluating headache intensity, while the latter measures the quality of life. The long-term effect deserves more attention than the frequent occurrence of headache. Therefore, our study period includes 4 weeks of treatment and 8 weeks of follow-up, in order to observe the long-term response.

TTH has immense public health costs, both in China and around the world, owing to its high prevalence among the general population, especially with regard to indirect costs (i.e., lost work and leisure time). As such, the economic costs are increasing. Data from a cross-sectional survey has shown mean annual costs of €303 per capita for tension-type headache in Europe [46]. Among them, the direct cost is €25, less than CNY 468 per person in China [47]. In order to assess costs and cost-effectiveness for patients taking XFZY compared with patients receiving placebo, we will calculate the health economic index as one of the outcome measures.

In conclusion, the results of this study are expected to provide evidence of high methodological quality on the efficacy and safety of XFZY for TTH.

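### The Introduction asks whether XFZY is superior to placebo on safety, but the only between-group safety analysis stated is a significance test of AE proportions, which cannot bound an excess risk

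*Protocol article*

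**What the plan says.** The Introduction closes with a single aim for both endpoints, to "investigate whether the efficacy and safety of XFZY for TTH patients with QBS is superior to placebo". The Discussion names safety again as something the trial will deliver: "the results of this study are expected to provide evidence of high methodological quality on the efficacy and safety of XFZY for TTH".

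Section 2.10 defines the safety population as "a safety analysis set with all subjects who took the drug at least once". It says that this set "will be adopted to detect whether the AE proportions are significant between the two groups", by a chi-square "test or Fisher's exact test". The general rule in the same section is "Two-tailed *p* values less than 0.05 will be considered statistically significant". No other comparison of safety between the arms is described.

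Section 2.9 sizes the trial on the VAS primary outcome alone: "A sample size of 87 patients per group was determined to provide 80% power to achieve statistical significance at the 5% 2-sided level". The article states no expected AE rate, no acceptable excess and no target precision for safety.

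Section 2.8 adds review of individual cases and monitoring: causality grading of AEs, laboratory tests and ECG at baseline and week 4, rapid reporting of serious adverse events (SAEs), and an independent Data and Safety Monitoring Committee (DSMC).

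**The concern.** The stated aim and the stated test do not fit together. Read literally, superiority in safety would require significantly fewer AEs on XFZY than on placebo. A two-sided test of equal proportions has three possible outcomes: significantly fewer AEs, significantly more, or no significant difference. The first would meet the aim and the second would signal harm. The article does not say what the third would mean. It does not meet a superiority aim, and a p-value at or above 0.05 does not show which excess risks the data rule out.

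This matters because, if AEs are uncommon, the third outcome is likely even when XFZY materially raises the AE rate. The safety half of the aim would then have no stated quantity on which to base a conclusion.

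**Working it through.** **Inputs.** From the article: 87 per group, two-sided 5%, chi-square or Fisher, and a safety set of everyone with at least one dose (so up to 87 per group). Assumed, because the article gives no AE rate: placebo AE proportions of 5%, 10%, 15% and 20%, with a doubling on XFZY. The article has no safety power or precision figure to reproduce. The 87 is taken as given; it belongs to the VAS calculation.

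**1. Chance of missing a doubling.** By normal approximation, with p̄ the mean of the two proportions and n = 87:

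z = [(p₂ − p₁) − 1.96·√(2·p̄(1 − p̄)/n)] / √[(p₁(1 − p₁) + p₂(1 − p₂))/n], and the miss probability is 1 − Φ(z).

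For 10% vs 20%:
- 1.96·√(2·0.15·0.85/87) = 0.1061
- √[(0.09 + 0.16)/87] = 0.0536
- z = (0.10 − 0.1061)/0.0536 = −0.114, so the miss probability is 54.5%.

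Exact enumeration of two independent binomials, adding up the probability of all tables with p≥0.05, gives:

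| Placebo vs XFZY | Missed, chi-square (uncorrected) | Missed, Fisher |
|---|---|---|
| 5% vs 10% | 77% | 84% |
| 10% vs 20% | 55% | 62% |
| 15% vs 30% | 33% | 40% |
| 20% vs 40% | 17% | 21% |

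If only 87 × 0.85 ≈ 74 per group contributed, the chi-square figures would be 78.5%, 59.5%, 40.5% and 23.1%, and the Fisher figures 87.4%, 68.3%, 48.1% and 29.5%. For scale, 80% power for the four doublings needs about 435, 199, 121 and 82 per group.

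**2. What a non-significant result leaves open.** Take 18/87 on XFZY and 9/87 on placebo, a difference of 20.69% − 10.34% = 10.34 percentage points.
- Chi-square: the pooled proportion is 27/174 = 0.1552, so χ² = 0.10345² / (0.1552 × 0.8448 × 2/87) = 3.55 and p = 0.06.
- Fisher: p = 0.09.
- Wilson 95% limits: 13.51% to 30.35% on XFZY, and 5.54% to 18.50% on placebo.
- Newcombe lower limit: 10.34 − √[(20.69 − 13.51)² + (18.50 − 10.34)²] = −0.5 points.
- Newcombe upper limit: 10.34 + √[(30.35 − 20.69)² + (10.34 − 5.54)²] = +21.1 points.

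Both permitted tests would report no significant difference, although the data are compatible with an excess of up to 21 points.

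**3. The same holds when the counts are equal.** With 9/87 in each arm, the simple 95% interval is ±1.96·√(2 × 0.1034 × 0.8966/87) = ±9.1 points. An excess of 9 points is not excluded, and the p-value of 1.0 does not show this.

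**The case against.** Several objections have force.

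- **No text says that a non-significant test means XFZY is safe.** A reader might infer that the plan intends this. The article does not support that inference: Section 2.10 states a test but no conclusion for p≥0.05, and under the Introduction's superiority aim such a result would be a failure to show the aim. This objection stands, and the point here is limited to the mismatch between aim and test.
- **The power figures depend on assumed rates.** This also stands. A reader might take the test to miss a doubling in most cases, or to become reliable only for something like a fourfold rise. Neither holds across the assumed range. Below a placebo rate of about 10% most doublings are missed, at 15% a minority are, and at 20% about one in six is by chi-square.
- **Trials are normally sized on efficacy.** True, and it is no fault here. Low power for AEs is a reason to estimate the difference rather than test it; it is not a reason to enlarge the trial.
- **Safety does not rest on the p-value alone.** Section 2.8 provides causality grading, laboratory and ECG checks, SAE reporting and DSMC review. These supplement the between-group comparison, but the article does not describe them as measuring the excess risk between arms.
- **Intervals may be in the analysis plan that Section 2.10 mentions.** They may, and their absence from an article would not by itself be a finding. What remains is what the article does state: a superiority aim for safety, and a significance test as the comparison serving it. The Discussion and Abstract put the aim more neutrally, so the Introduction's wording may be loose drafting, but it is the wording that states the aim.

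**Conclusion.** The point holds in a limited form. The safety aim is worded as superiority, and the one between-group analysis described is a significance test. A non-significant result would neither meet that aim nor limit the excess AE risk. How often a real doubling would go undetected depends on a placebo AE rate that the article does not give. Across assumed rates of 5% to 20% with 87 per group, it is 77% falling to 17% by uncorrected chi-square, and 84% falling to 21% by Fisher. The worked example shows an excess of up to 21 percentage points left open by a result labelled not significant. This is a correction of wording and method that should be made. It does not show that the sample size is wrong for its purpose or that safety monitoring is inadequate.

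**What to change.** **Section 2.10.** Make the between-group safety comparison the risk difference, XFZY minus placebo, with its 95% confidence interval (for example Newcombe) in the safety set. Report it for any AE, for drug-related AEs using the causality grading in Section 2.8, and for SAEs. Keep the chi-square or Fisher p-value as descriptive. Add a sentence that p≥0.05 will not be taken as evidence of no excess risk.

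**Introduction.** Limit superiority to efficacy, and restate the safety aim as estimating the excess risk of AEs with XFZY over placebo.

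**Cost.** Wording changes and one interval per AE category, from data already collected. No extra patients, visits or procedures are needed. The downside is a more cautious safety statement, because the intervals will be wide at this sample size.
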